#### Methods to prevent and monitor missing data

We will use several strategies to prevent and reduce missing data, particularly trial outcome measures. We will use REDCap [165] for data collection and entry. REDCap is a secure, HIPAA-compliant, widely used web-based research application that supports calculations and branching logic programming. It provides (1) an intuitive interface for validated data entry, (2) audit trails for tracking data manipulation and export, (3) automated export procedures for seamless data downloads to common statistical packages, and (4) tools for importing data from external sources. We will program our REDCap database to require responses to all survey and interview questions and real-time documentation of reasons for missing data. Reasons for truly missing data (e.g., if participants are uncomfortable completing specific items) will be completed at the time of data collection and documented during data entry. This will also reduce missing data due to data entry errors. The trial data management protocol will include immediate post-data entry notifications, tracking of rectifications of missing data, and daily review of new data entries with immediate notification to data entry personnel and site coordinator for rectifications needed for missing data. We will attempt to complete trial outcomes at protocol-specified assessment times on all randomized persons, even those who have dropped from the study. Our project analyst will review data weekly to ensure completeness; a weekly report to investigators and study coordinators will identify outstanding missing data that needs to be completed, as well as a time field indicating number of days since the missing data query was first generated. The study protocol will provide instructions for use of these strategies and procedures.

#### Data management

We will employ a detailed data management plan to ensure the integrity and accessibility of study data. We will store all data on secure servers in an integrated REDCap database [164, 165]. All clinical, behavioral, and demographic information for each participant will be entered into the database. We will use REDCap to create a web-based data entry interface, perform Stage 1 and Stage 2 randomizations, update participant information, manage baseline and follow-up visits, and track participant status, and to export data efficiently in various self-documenting forms directly into SPSS, SAS, R, or Excel using REDCap’s de-identification option, thereby ensuring that exported data are complete, self-explanatory, and de-identified. We will also design and implement a database system to acquire and integrate all paper and electronic files from participant assessments. We will implement procedures to maintain data integrity, reliability, security, and accessibility, ensuring that all data are consistent with HIPPA and other federal regulations and with applicable policies of our local IRBs. We will ensure that all participant data have been transmitted and incorporated into the central database, and fully documented, in a timely manner. We will also manage and document data requests, make data available to investigators through a Data Use Agreement, and maintain archives of all analysis datasets and datasets provided to other investigators.

##### Tracking system

The study's REDCap database will aid study coordinators and participating sites in tracking participant visits and data collection. The password-protected, structured web-based portal will include real-time reports to identify participants who are due for a follow-up visit, list the type of data to collect in that visit, and list any information that has been missing from past visits. All data modifications will be logged to maintain accountability for all entries and edits. Automatic monthly emails will be sent to investigators and coordinators alerting them to upcoming visits of their participants.

##### Security

We will ensure the database systems, data access policies, and data transmission protocols exceed HIPPA regulations and data security standards for IRBs. Only designated staff will have direct access to the database. The front-end web portal to the database will be accessible to all investigators and study coordinators. The REDCap server is housed behind multiple firewalls in a locked and guarded USC data center equipped with security cameras and intrusion detection systems that is staffed by security at all times. All electronic connections to the REDCap environment are encrypted. Only system administrators at the data center are authorized to access the back-end database server directly by logging into a virtual private network. We will institute policies that (a) temporarily deactivate user accounts that have not logged into the system within a specified time; (b) automatically require staff to change passwords at regular intervals; (c) match current users against current study staff, and terminate user accounts for staff who no longer are associated with the project; and (d) institute independent audits at regular intervals by our ISO to assess HIPPA compliance and security. All data files transmitted to investigators will be encrypted and password-protected at the highest level of data encryption, then transmitted via a secure File Transfer Protocol. The password used to encrypt the file will be transmitted separately from the file.

### Sample size and power

SMART designs are commonly but incorrectly assumed to require prohibitively large sample sizes [54]. It is common to think, for example, that data from a study design such as ours will be analyzed in a 6-way ANCOVA that compares outcomes across all 6 subgroups, which would indeed likely require a large sample size. That analysis, however, does not correspond with our primary aims and hypotheses, which are tested as two main effects and their interaction, and which require a sample size considerably smaller than for a 6-way ANCOVA [54]. We have made it our priority to identify a sample size that will allow us to test Stage 2 effects with sufficient power. We obtained the estimates of effect size (ES, in SD units) required for estimating our required sample size as follows:

(1) We used treatment ESs from the CAMS efficacy trial, which compared combined medication+CBT to monotherapies (medication alone, CBT alone) and placebo. CAMS reported quantitative anxiety outcomes using the Pediatric Anxiety Rating (PARS) scale. Outcomes did not differ significantly in CBT alone vs medication alone (though group mean differences on the PARS slightly favored medication over CBT). However, CAMS did find large ESs for combined medication+CBT compared to monotherapy, with a somewhat larger difference compared to CBT alone than medication alone.

(2) Using augmented CBT in CBT non-responders as the base, relative ESs reported at 24 weeks in CAMS were used as ES estimates for CBT + medication (i.e., medication added to CBT), medication alone, and medication+CBT (i.e., CBT added to medication). For Stage 1 remitters, we used an ES of 0.2 above their non-remitter counterpart.

(3) Group main effect ESs were then computed for a Stage 1 remission rate of 40%. Our estimated Stage 1 remission rate of 40% is a conservative estimate based on the CAMS remission rate of 35% achieved for ethnic minorities, when applying remission criteria less stringent than ours [30]. In CAMS, the 12-week remission rate was also approximately 10% higher in medication-only compared to CBT-only. We used this 10% difference in these calculations to compute ESs and resulting sample size estimates. For Main Effect 1 (start with medication vs start with CBT), ESs for all 3 medication or CBT groups (1: remitter; 2: non-remitter➔optimize monotherapy; 3: non-remitter➔medication+CBT) were computed as a weighted average of the group-specific ESs. Weights were the remission rate, with the non-remitter weight (1 minus remission-rate) split equally among the 2 randomized non-remitter groups (reflecting 1:1 Stage 2 randomization among non-remitters). For Main Effect 2 (among Stage 1 non-remitters, optimize Stage 1 treatment vs add the other treatment), ESs were computed as a weighted average of the ESs for monotherapy optimizers (medication+, CBT+) and a weighted average of the combined (medication+CBT, CBT + medication) groups. These weights were again 0.5*(1- remission-rate).

[4] We then computed the sample size required to detect Main Effect 2 (optimize monotherapy vs add the other therapy in non-remitters) at 80% power and tested at a 2-sided alpha = 0.05. From our computations above, the Main Effect 2 ES was approximately 0.40 SD, requiring a sample size of 194 participants among Stage 1 non-remitters. Increasing the sample size of 194 by the non-remission rate (N divided by non-remission rate) and by the estimated 20% dropout rate, yielded a sample size of 404 (202 per group) for Stage 1 remission rates of 40%. Randomizing 404 participants, with an estimated 324 finishing the trial and a remission rate of 40%, will provide the ability to detect an overall Main Effect 1 (medication first versus CBT first) ES of ≥0.31 SD with 80% power.

#### Power analyses for telehealth-based treatment delivery

The above effect size estimates used the CAMS 24-week trial results to estimate comparative effect sizes for the 6 groups (remitters, non-remitters augment Stage 1 intervention; non-remitters add intervention). Two RCTs provide data to estimate effect size estimates for treatment delivery via telehealth. The first [195] is a meta-analysis of 26 RCTs comparing videoconferencing-based telehealth vs in-person delivery of psychiatric services, which included both pharmacotherapy and psychotherapy. The summary effect size (telehealth vs in-person) = − 0.11 (95% CI -0.41, 0.18), a non-significant difference with the direction of effect favoring tele-health delivery. The second [196] is an RCT comparing telehealth vs in-person CBT over 24 weeks (the same duration as our study) in 115 youth with adolescent anxiety disorder. For consistency with our sample size calculations (which used the primary outcome from the CAMS trial, the clinician-rated Pediatric Anxiety Rating Scale), we estimated the effect size for the Clinician Severity Rating outcome measure, which was 0.05 (95% CI -0.77, 0.95). This is a non-significant difference, with the direction of effect favoring in-person CBT. We used these estimated in-person vs telehealth effect sizes to estimate adjustments to our original effect sizes, adding 0.11 to all of the medication group effects (medication remitter, medication non-remitter: augment, medication non-remitter add CBT), and subtracting 0.05 from all the CBT group effects (CBT remitter, CBT non-remitter: augment, CBT non-remitter: add medication). We concluded that there is no effect on the overall main effect 2 effect size used to estimate sample size, because the main effect 2 comparison is: Augment (Medication+; CBT+) vs Add (Medication, add CBT; CBT, add Medication), and the adjusted remote effects appear in both Augment and Add groups, so these effects cancel out. The same conclusion is obtained if we separately consider ONLY a remote medication effect, or ONLY a CBT effect.

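### Telehealth effects cancel out of Main Effect 2 only because the treatment added in Stage 2 is given no telehealth adjustment; the claim should be conditional

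*Protocol article*

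**What the plan says.** Under Sample size and power, the trial is sized on Main Effect 2, which compares optimizing the first treatment with adding the other one among Stage 1 non-remitters. The article states that "the Main Effect 2 ES was approximately 0.40 SD, requiring a sample size of 194 participants among Stage 1 non-remitters", "at 80% power and tested at a 2-sided alpha = 0.05". Dividing by the non-remission rate and allowing for 20% dropout gives 404.

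The section Power analyses for telehealth-based treatment delivery then asks whether remote delivery changes that effect size. It adjusts by "adding 0.11 to all of the medication group effects" and takes 0.05 from all the CBT ones. The listed medication groups include the one that adds CBT, and the listed CBT groups include the one that adds medication. Each child's adjustment therefore follows the Stage 1 treatment. The section reasons that the adjustments occur in both the Augment and the Add groups, "so these effects cancel out". It continues: "The same conclusion is obtained if we separately consider ONLY a remote medication effect, or ONLY a CBT effect".

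Two other places matter. The Stage 2 description under Study design and the Figure 5 caption define the Add arms as combined medication and CBT. The section In-person and telehealth treatment allows either treatment to be delivered remotely and says that, at study initiation, all sites provide all non-emergency mental health care that way.

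**The concern.** A medication-first child in the Add arm receives CBT, and the Augment comparator does not. A CBT-first child in the Add arm receives medication, and that comparator does not. If remote delivery changes what a treatment achieves, the change in the added treatment occurs in the Add arms only, and nothing in the Augment arms offsets it. The adjustment that does cancel belongs to the treatment both arms share.

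The sentence on single effects shows this most clearly. If remote CBT is 0.05 SD weaker and medication is unaffected, adding remote CBT to medication brings 0.05 SD less, while optimized medication alone is unchanged. That lowers the contrast.

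Main Effect 2 sets the sample size, and this section is the stated ground for saying that telehealth leaves it untouched. A reader relying on it would believe that every scenario it names keeps the planned power.

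**Working it through.** **Inputs from the article.** Main Effect 2 of about 0.40 SD; two-sided alpha 0.05; target power 80%; 194 non-remitters randomized 1:1 (97 per arm); remission 40% with a 10-point advantage for medication; dropout 20%; telehealth adjustments m = +0.11 (medication) and c = -0.05 (CBT).

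**Assumptions.** Telehealth effects add in combined treatment, all care is remote, and the point estimates are true. The shares of non-remitters who began with each treatment are either equal (0.5 and 0.5) or follow 45% remission on medication and 35% on CBT. That split is one reading of a 40% average with a 10-point difference: 0.55/(0.55+0.65) = 0.458 medication-first and 0.542 CBT-first.

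**Reproducing the plan.** The normal formula 2(1.96+0.842)²/0.40² gives 98.1, so 99 per arm or 198, within 3% of 194. With 97 per arm, 80% power is reached at 0.402 SD, which fits an effect of approximately 0.40. Then 194/0.6/0.8 = 404.2. Power at 0.40 SD is Φ(0.40·√(97/2) - 1.96) = Φ(0.826) = 79.6% (79.2% by the t distribution).

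**The plan's assignment.** Writing w for the medication-first share, Augment and Add both shift by w·m + (1-w)·c. The difference stays at exactly 0.40 for any m and c, so the cancellation follows from the labelling.

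**Adjustment applied to every arm that receives the treatment.** Medication-first Add also receives c, and CBT-first Add also receives m. Hence

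Main Effect 2 = 0.40 + (1-w)·m + w·c.

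| Telehealth effect | Equal weights: effect (SD) | Power | 45%/35% remission: effect (SD) | Power |
|---|---|---|---|---|
| Both | 0.40 + 0.055 - 0.025 = 0.430 | 85.0% | 0.40 + 0.060 - 0.023 = 0.437 | 86.0% |
| Medication only | 0.40 + 0.055 = 0.455 | 88.7% | 0.40 + 0.060 = 0.460 | 89.3% |
| CBT only | 0.40 - 0.025 = 0.375 | 74.3% | 0.40 - 0.023 = 0.377 | 74.7% |

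The t distribution lowers each power by about half a point or less. For 80% power, the CBT-only case would need 222 to 224 non-remitters by the same formula that gives 198 at 0.40 SD. The both-effects case would need 166 to 170.

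**A different rule.** If combined-treatment children receive the average (m + c)/2 instead of the sum, the net shift with equal weights is zero in all three scenarios. With weights 0.458 and 0.542 the residual is about +0.007 SD (both), +0.005 (medication only) and +0.002 (CBT only).

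**Main Effect 1.** Under the plan's assignment the shift toward medication is 0.11 + 0.05 = 0.16 SD. Under the corrected assignment with 45%/35% remission, the Add shares are 0.275 and 0.325, and the shift is (0.11 - 0.275×0.05) - (-0.05 + 0.325×0.11) = 0.096 + 0.014 = 0.11 SD.

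**The case against.** The strongest reply is that the section makes no arithmetic slip. Given its rule, the terms do cancel, including when either one is set to zero. The dispute is over the rule, and full additivity is not in the article either. Averaging the two effects in combined arms would nearly restore cancellation. Stacking is also open to question on the source: the 0.11 comes from a meta-analysis that mixed pharmacotherapy and psychotherapy, so adding it to a separate CBT effect may count psychotherapy partly twice.

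Much of this stands. The power figures are conditional, and the additivity assumption must be stated with them. The reply does not rescue the text, however. The article neither states nor uses an averaging rule. Its actual rule gives the added treatment no telehealth effect at all, although that treatment may be remote and is what distinguishes the two arms.

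It is also fair that the shifts are small beside the cited 95% confidence intervals (-0.41 to 0.18, and -0.77 to 0.95). The article expects a mix of remote and face-to-face care after the pandemic, so the full shifts are upper limits for these point estimates.

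A reader might also infer that telehealth builds an artefact worth half the detectable 0.31 SD into Main Effect 1. The documents do not support that. The 0.16 SD arises under the same assignment that is questioned here; the corrected figure is about 0.11 SD. Remote care is deliberately part of the effectiveness being compared, so this is a contribution of delivery mode. Telehealth covariates and a moderation analysis are already planned under Effects of treatment modality and HTE analysis plan. The telehealth section addresses the effect size behind the sample size, so its silence on Main Effect 1 is not in itself an error.

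**Conclusion.** The concern holds as a correction to two sentences. The statement that telehealth drops out of Main Effect 2, with both effects or with either alone, depends on leaving out the telehealth effect of the added treatment. With each adjustment applied wherever that treatment is given, the effect ranges from about 0.38 to 0.46 SD and power at 194 non-remitters from about 74% to 89%. This rests on additivity, fully remote care and true point estimates; the result hardly differs between equal and 45%/35% remission weights.

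A reader might infer that the trial is underpowered or that 404 is wrong. The figures do not show that. In the plan's main scenario, with both effects, power rises to about 85-86%. Only the CBT-only case falls short of 80%, by about 5 to 6 points, and it rests on a 0.05 SD estimate with a very wide interval.

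**What to change.** Replace the cancellation sentence and the sentence on single effects. The new text should say that the shared first treatment's adjustment cancels and the added treatment's does not. It should state the additivity assumption and give the conditional figures: about 0.43-0.44 SD (power about 85-86%) with both effects, 0.46 SD (about 89%) with the medication effect only, and 0.38 SD (about 74-75%) with the CBT effect only. It should add that averaging the two effects in combined arms would nearly restore cancellation, and that the cited confidence intervals are far wider than these shifts. If Main Effect 1 is mentioned, report a delivery-mode contribution of about 0.11 SD toward medication under the corrected assignment (0.16 SD under the plan's own).

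The cost is a few sentences and one less favourable power figure. Sample size, randomization and analyses stay as they are.

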### Data analysis plans

Upon completion of the final trial participant, we will complete a final database review and finalize data queries, then lock the trial database for final analysis. To evaluate baseline comparability, we will compare demographic and clinical characteristics, and trial outcome measures, at baseline between treatment groups. Continuous baseline measures will be summarized by mean (SD) or median (IQR), and categorical measures by frequency (percent). Standardized group differences will be computed and presented for all baseline variables.

We will conduct an intent-to-treat analysis, by which subjects will be analyzed according to randomized intervention, consistent with standard practice in clinical trials. Distributions of outcome variables will be graphically examined; normalizing transformations will be applied if needed. The 24-week continuous measures of primary and secondary trial outcomes will be compared between treatment groups using general linear models, with the 24-week measure as the dependent variable. SMART design groups will include Stage 1 randomized group and Stage 2 randomized group. The randomization stratification factors (age group,clinical site, and dichotomized baseline parent SCARED-41), as well as baseline measures of the trial outcome (Youth SCARED ratings), will be included as model covariates. Results will be summarized by treatment group means (SDs) and mean treatment group differences (and 95% confidence intervals). No interim analyses are planned.

To **test Main Effect 1**, a 2-group (Stage 1 randomization) analysis of covariance will be used, comparing subjects randomized to medication first to those randomized to CBT first [53, 54, 197]. To **test Main Effect 2** among Stage 1 non-remitters, a 2-group analysis of covariance will also be used, comparing (a) non-remitting subjects randomized at Stage 2 to optimization of their Stage 1 monotherapy, vs (b) non-remitting subjects randomized at Stage 2 to combination treatment (medication+CBT or CBT + medication) across levels of Stage 1 randomization. Finally, to test whether one sequence of treatment modalities (CBT➔CBT; CBT➔med; med➔med; med➔CBT) is significantly better or worse than predicted from the two main effects, an interaction term of Stage 1 randomization with Stage 2 randomization will be added to the model. The addition of the interaction term will allow estimation and testing of each of the 4 treatment sequences [53, 54, 197].

To reflect the SMART design, two additional analytic issues must be addressed. First, the comparison of 4 sequences requires replication of the Stage 1 remitters, to reflect these subjects’ contributions to both the Stage 2 augmentation and combination treatment strategies (i.e., each Stage 1 remitter contributes 2 observations to this analysis). Second, to reflect the fact that Stage 1 remitters are only randomized once, whereas Stage 1 non-remitters are randomized twice, regression weights will be used, such that each subject is weighted by the inverse probability of ending up in the sequence to which they were randomized (weight of 2 for remitters, 4 for non-remitters). As the Stage 1 remitters contribute two observations to these analyses (and thus correlated outcomes) in comparing treatment sequences, a sandwich-based variance estimator will be used to obtain robust standard errors for effect estimates [53, 54].

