### Study design

This will be a single-blind [126, 127] SMART design [51, 52] of 24-week treatment duration that will employ two sequential levels of randomization, one in each of two 12-week stages of the study **(**Fig. 2**)**.

#### Stage 1

404 children ages 8–17 who have an anxiety disorder will be randomized 1:1 to receive 12 weeks of either the medication fluoxetine in upward-titrated dosages or weekly CBT implemented using the *Coping Cat* CBT model [128].

#### Stage 2

All participants who do not remit in Stage 1 will be randomized 1:1 to either (1) optimization of their Stage 1 treatment, or (2) optimization of their Stage 1 treatment and addition of the other treatment modality (Fig. 2). Study assessments will be obtained at baseline, week 12, and week 24. A small subset of measures (SCARED-41, and the Pediatric Side Effect Questionnaire) will also be obtained at weeks 6 and 18. Participants who remit during the first 12 weeks of treatment will continue maintenance-level therapy with the single-modality treatment received in Stage 1. If a participant who achieved clinical remission during the first 12 weeks of treatment relapses at the week 18 study assessment (defined as having a SCARED total score of ≥25), the participant will be referred to the treating clinician to restart or slightly intensify the previous treatment assigned in Stage 1 of the study. Following conclusion of the 24-week trial, we will follow and obtain all the same study assessments in all participants quarterly for at least 12 months [44, 126, 127].

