#### Randomization

In each randomization within trial Stages 1 & 2 **(**Fig. 5**)**, eligible and consenting/assenting participants will be randomized in a 1:1 allocation to the 2 treatment regimens. Randomization will be stratified by study site, age group [8–17], and baseline symptom severity (dichotomizing SCARED-41 scores as ≤33 or > 33, based on the median SCARED-41 score for participants having scores ≥25 in the CAMS [49] and LAMS [163] studies). Randomization will be further blocked, with a relatively small block size to ensure balanced randomization over the short term; block size will not be revealed to investigators or trial staff. The study statistician will develop and monitor fidelity to the randomization sequence. At the conclusion of week 12 of the Stage 1 intervention (medication vs CBT), anxiety symptoms and functional impairment will be reassessed. Participants who meet criteria for remission will continue maintenance-level therapy with the single-modality treatment received in Stage 1; non-remitting participants will complete Stage 2 randomization. The REDCap (Research Electronic Data Capture) randomization module will be used to randomize patients to study treatments [164, 165]; the study statistician will develop the stratified blocked randomization sequences. The randomization sequence will not be viewable. Randomization capability will be limited to the lead research coordinator and study statistician; randomization will only be available following confirmation that informed consent has been completed and all trial inclusion and exclusion criteria are met. Treatment assignment will be communicated from the lead research coordinator to the study coordinator who is assigned to screen, enroll, and administer assessments to that participant.

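### The Main Effect 2 ANCOVA adjusts for study-entry Youth SCARED but not for the week-12 score taken before Stage 2 randomization, so it gives up available precision

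*Protocol article*

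**What the plan says.** Data analysis plans gives one covariate set for the general linear models of the 24-week outcome: age group, site, dichotomized baseline SCARED, "as well as baseline measures of the trial outcome (Youth SCARED ratings), will be included as model covariates". For Main Effect 2, "among Stage 1 non-remitters, a 2-group analysis of covariance will also be used", with no covariate list of its own. Baseline there means study entry, since Study design and Table 2 treat baseline and week 12 as separate assessments.

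The Randomization section states: "At the conclusion of week 12 of the Stage 1 intervention (medication vs CBT), anxiety symptoms and functional impairment will be reassessed". Non-remitters are then randomized. The remission criteria under Study design, Stage 2 use the youth SCARED-41 total, its single-disorder thresholds and the CAIS.

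Sample size and power makes Main Effect 2 the sizing contrast ("We then computed the sample size required to detect Main Effect 2", "at 80% power and tested at a 2-sided alpha = 0.05") and reports that "the Main Effect 2 ES was approximately 0.40 SD, requiring a sample size of 194 participants among Stage 1 non-remitters".

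Prior outcome values are used in the imputation models (Statistical methods to address missing data), but no week-12 value is named in the Main Effect 2 model.

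**The concern.** Stage 2 is a new randomization, and its own baseline is week 12. The week-12 Youth SCARED is measured before that randomization. Everyone classified as a non-remitter should have it, and it lies 12 weeks from the endpoint rather than 24. The study-entry score is 12 weeks older and was taken before a treatment to which participants respond differently.

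The design does not compensate. Randomization in both stages is stratified on severity at study entry, so neither allocation nor analysis controls severity at entry to Stage 2.

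At stake is the width of the interval for the contrast with the fewest participants, about 194 against about 324 for Main Effect 1.

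**Working it through.** **1. The plan's own figure.** Inputs from Sample size and power: 0.40 SD, two-sided alpha 0.05, 80% power, 40% remission, 20% dropout; Stage 2 allocation is 1:1.

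- n per arm = 2(1.960 + 0.842)² / 0.40² = 98.1, so 99 per arm or 198 in total, against 194 stated.
- Power with 97 per arm = Φ(0.40/√(2/97) − 1.960) = Φ(0.826) = 79.6%.
- 194 / 0.60 / 0.80 = 404.2, matching 404.

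The figure reproduces to within about 2%, with no covariate in it.

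**2. Assumed inputs.** The documents give no correlations. Among all randomized participants, with unit variances, take b = r(baseline, week 24) = 0.3–0.5, c = r(baseline, week 12) = 0.3–0.6 and d = r(week 12, week 24) = 0.5–0.7. Remission is 20% to 40%, approximated as the lowest 20% or 40% of a normal week-12 score. The actual rule also uses disorder thresholds and the CAIS.

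**3. Restriction to non-remitters.** Let p be the remission rate, a = Φ⁻¹(p), λ = φ(a)/(1 − p) and h = λ² − aλ. The week-12 variance falls to 1 − h. At p = 0.40, h = 0.578; at p = 0.20, h = 0.417. Among non-remitters:

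- V24 = 1 − d²h; V0 = 1 − c²h; Cov(0,24) = b − cdh
- Residual variance, baseline only: Vb = V24 − Cov(0,24)²/V0
- Residual variance, baseline and week 12: V2 = 1 − (b² + d² − 2bcd)/(1 − c²)

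**4. Central case (b, c, d) = (0.4, 0.5, 0.6) at 40% remission.**

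- V24 = 1 − 0.36 × 0.578 = 0.792; V0 = 1 − 0.25 × 0.578 = 0.856; Cov = 0.4 − 0.30 × 0.578 = 0.227
- Vb = 0.792 − 0.227²/0.856 = 0.732
- V2 = 1 − (0.16 + 0.36 − 0.24)/0.75 = 0.627
- Ratio 0.627/0.732 = 0.856, a cut of 14%; 194 participants are worth 194/0.856 ≈ 227.
- With 0.40 in units of √V24, power is Φ(0.40/(s√(2/97)) − 1.960). Baseline only: s = √(0.732/0.792) = 0.961, giving 82.6%. With week 12: s = √(0.627/0.792) = 0.890, giving 87.9%.

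**5. Other combinations**, with 194 held fixed:

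| b, c, d | Remission | Variance cut | Power, baseline only → plus week 12 | Effect detectable at 80% power (SD) |
|---|---|---|---|---|
| 0.5, 0.6, 0.5 | 40% | 5% | 85.9% → 87.4% | 0.369 → 0.361 |
| 0.5, 0.6, 0.5 | 20% | 6% | 87.0% → 88.9% | 0.363 → 0.352 |
| 0.3, 0.4, 0.5 | 40% | 10% | 81.3% → 85.1% | 0.393 → 0.374 |
| 0.4, 0.5, 0.6 | 40% | 14% | 82.6% → 87.9% | 0.387 → 0.358 |
| 0.4, 0.5, 0.6 | 20% | 18% | 83.5% → 90.0% | 0.382 → 0.345 |
| 0.5, 0.6, 0.7 | 20% | 26% | 85.8% → 94.0% | 0.370 → 0.319 |
| 0.3, 0.5, 0.7 | 20% | 34% | 80.9% → 93.7% | 0.396 → 0.321 |

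The corner (0.3, 0.6, 0.7) at 20% remission gives 37%. It needs a baseline to week-24 correlation well below the product of the other two (0.6 × 0.7 = 0.42), so it is the least plausible set. Variance fell in every combination tried.

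**The case against.** **Nothing planned fails.** This stands. Stage 2 is randomized, so the estimate without week 12 is unbiased. The 194 is an unadjusted calculation, so adjusting for study-entry SCARED should already add something to the planned power. A reader might infer that Main Effect 2 is underpowered or biased, and the documents support neither.

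**The gain is uncertain.** This stands too. It rests on assumed correlations, and restriction to non-remitters narrows the week-12 range and weakens its correlation with week 24. If study-entry SCARED predicts week 24 as well as week-12 SCARED does, the gain is only about 5% or 6%.

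**Week 12 does not belong in every model.** This stands and limits the fix. A reader might infer that all the Stage 2 models need it. But the interaction term is also meant to yield estimates for the four sequences, in a weighted analysis with remitters replicated, and those include comparisons between CBT-first and medication-first sequences. For these, as for Main Effect 1, week 12 is an outcome of the Stage 1 randomization. Conditioning on it removes the Stage 1 effect carried through week 12 and can bias what remains.

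**Stage 1 arm may already be in the model.** A reader might infer that it is omitted, because the 2-group ANCOVA does not name it. The same section says the design groups include the Stage 1 group and that Main Effect 2 is taken across Stage 1 levels. The wording is terse and needs confirming, but it is not a clear omission.

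**Covariates are detail for the analysis plan.** This stands in part. An unseen plan may add week 12. The article, however, does not leave the list open: it names the baseline value as the only prior outcome measure.

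**Conclusion.** The point holds as one of efficiency, confined to the non-remitter analysis of Main Effect 2. A valid and more recent pre-randomization measure is collected but left out of the listed covariates for the contrast that sized the trial.

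Under the stated assumptions the loss is about 5% to 34% of residual variance. In the central case it is 14% to 18%, or roughly 5 to 7 percentage points of power for 0.40 SD. The direction follows from the design; the size depends on correlations that the documents do not give. It is worth changing because the change is nearly free, not because the trial would otherwise miss its stated power.

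**What to change.** Before any unblinded analysis, give Main Effect 2 its own covariate list:

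- Add the week-12 value of the outcome being analyzed: Youth SCARED for the primary outcome, and each secondary outcome's own week-12 value.
- Keep study-entry SCARED and the stratification factors.
- Confirm that Stage 1 arm is a term. In this model it is an adjustment term, not an estimate of the Stage 1 effect.
- Use the same list for any Stage 1 by Stage 2 interaction test confined to non-remitters.
- State that week-12 values do not enter Main Effect 1 or the weighted, replicated comparison of the four sequences.

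The cost is a sentence or two in the analysis plan, with no new data or visits. Participants lost before Stage 2, whom the plan assigns non-remitter status and carries into multiple imputation, need an imputed week-12 value. The planned time-ordered imputation already covers missing outcomes and covariates at each time point.
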